#### Intervention

The intervention implementation of the post-CS home care guide will follow the CFIR framework, specifically on the implementation process by considering four factors, namely: planning, engaging, executing, and reflecting and evaluating [27]. In the planning stage, the researcher will meet with DRRH management to explain the purpose and schedule of the intervention. After the meeting with the management, the researcher will engage the nurse in charge of the wards on how to execute the training and mobilise nurse midwives and post-CS mothers.

*Assessment and education of post-caesarean mothers*. Before the intervention, the pre-tested tool will be used by the researcher and RA to assess baseline knowledge of post-CS mothers on home care after CS. Both the assessment and intervention of post-CS mothers will be done before discharge. The education intervention about home care will be given in one group depending on the number of post-CS discharged on that day. The intervention will involve slides projection of the post-CS home care and distribution of leaflets with simplified Swahili language and pictures demonstrating recommended home practices after CS. This will be followed by the questions and answers session for more clarification. The intervention will take about 1 hour including a question-and-answer session. This will be performed every day before discharge until the sample size is met. The researcher and other RA (nurse midwives in the profession) will be providing this education to post-CS mothers to ensure the home care guide after CS is delivered effectively. Thereafter, the participants will be instructed to come for the usual recommended post-natal visits to the same facilities for follow-ups that is, on the 7^th^, 14^th^ and 30^th^ day. On the 7^th^ day post-delivery, mothers will be instructed to come for stitch removal, assessment of the wound and other routine post-natal check-up services. In all visits, the post-CS mothers will be requested to report their practices at home, and assess their haemoglobin level to establish their anaemia status using the WHO classification [45]. For the purpose of this study, mothers will be instructed to come down to the facility on the 30^th^ day post-CS to evaluate their prognosis, to assess wound healing and their recovery in general. The wound assessments will be performed by two researchers and research assistants to minimise observer bias. For all wounds with SSI, their samples will be taken for culture to confirm the diagnosis. On the same day (30^th^-day post-delivery), a post-interventional assessment of the knowledge of post-CS home care will be done [46], after being exposed to the home environment.

*Assessment and training of nurse midwives*. The intervention by nurse-midwives will be followed after the intervention of the post-CS woman. They will also be trained in a written post-caesarean home care guide and its use the guide to educate post-natal mothers. Before the training, the pre-tested tool will be used to assess the baseline knowledge of nurses on post-CS home care. Thereafter, nurse midwives will be trained on the component and content of the guide and how they would use the guide to educate post-CS mothers. The intervention will be done in the hospital environment (meeting room) to ensure maximum participation of the study participants. The session will involve lecturing and lecturing discussion. The intervention will involve two training sessions scheduled on two different days since it is difficult to get all of the nurse-midwives in one day. The intervention will take three hours including the time for pre-interventional assessment. Thereafter, they will be post-tested on the same day. After the intervention, nurse midwives working in the post-natal ward will be required to provide home care education intervention to post-CS mothers, for making this intervention sustainable.

At SRRH, the control group of nurse midwives and post-CS mothers will not be exposed to the content of the developed home care guide. Nurse midwives will continue to provide their usual care to post-CS mothers at the facility. The control group will also be assessed for baseline knowledge of home care after CS. Post-CS mothers will be assessed first, they will be assessed for baseline knowledge about home care after hospital discharge before discharge, as in the interventional group.

Knowledge of participants on home care after CS and SSI status will be compared between the intervention and control group. To ensure equal treatment of both groups, nurse midwives in the control group will be trained on the post-CS home care guide and how to deliver the content to post-CS mothers after meeting the sample size of post-CS, where they will also be required to train post-CS mothers to ensure the sustainability of the intervention. The implementation of the intervention has been described in the Fig 3.

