The Enhanced Recovery After Surgery (ERAS) Society’s guidelines for postoperative care after CS recommends sham feeding, prevention of nausea and vomiting, provision of analgesics, nutritional care, glucose control, thromboembolism prophylaxis, early mobilisation, urinary drainage and discharge counselling on home care [21]. The guidelines emphasise discharge counselling on home care for post-CS mothers. However, it does not provide clear and detailed instructions on the same. The authors of these guidelines also admit a paucity of studies addressing optimal counselling recommendations for post-CS care [21]. In Tanzania, there are no guidelines available for post-CS home care and published studies reporting care of mothers at home after caesarean section deliveries are lacking. Guidelines to instruct care at home are critical because most post-caesarean section mothers are typically discharged home within 48 hours [16, 22] to avoid overcrowding of the hospitals. Further home visits by a nurse midwife for monitoring the progress of the post-CS woman after discharge is uncommon. Therefore, family members at home are primarily involved in the care of mothers and babies. This is contrary to developed countries, where home visits and surveillance for post-CS mothers are routinely conducted [13]. Studies report a complete lack of or less information regarding home care after CS compared to home care after vaginaly delivery [23, 24]. The limited available information about home care after CS highly varies among different sources across the region [25]. Post-discharge instruction, especially for post-CS mothers has been a neglected aspect of post-CS care for a long time [21]. Even the existing advanced guidelines worldwide are severely lacking [16, 21].

The government of Tanzania has upgraded and established more than 400 health centres in the country to provide Comprehensive Emergency Obstetric and Newborn Care (CEmONC) services, thereby increasing access to CEmONC services. With increased access to CEmONC services and early discharge of post-CS mothers, it is estimated that the need for post-CS care will increase. Therefore, the availability of a standard post-CS home care guide to provide guidance to post-CS mothers is of paramount importance. The use of a post-CS home care guide is expected to improve the knowledge of post-CS mothers and nurse midwives on home care after CS, and ultimately reduce post-CS complications including SSI in the country.

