### Conceptual framework

The self-care deficit theory [26] and Consolidated Framework for implementing Research (CFIR) [27] will guide the study. The self-care deficit model emphasises offering assistance to clients who can not care for themselves. The self-care can either involve total compensation, partial compensation, or education and support (total compensatory system, partially compensatory and educative-developmental system) [26, 28]. This study will focus on the education developmental system of the model that post-CS mothers should implement in order to manage their health through the instructions on care to be provided at home after CS.

The Consolidated Framework of Implementation Research (CFIR) consists of five domains; 1. Intervention 2. Inner environment 3. Outer environment 4. The individual involved in the intervention and 5. The implementation process of the intervention [27]. In this study, the intervention involves training nurse midwives and educating post-CS mothers. The inner environment is post-CS ward where education intervention will primarily take place and the outer environment is a post-CS mother’s home environment, the place to implement the recommended home care practices. The implementation process will involve training nurse midwives first about the guide followed by the provision of education to post-CS mothers on home care by the trained nurses [27]. All the above-mentioned domains are needed for the effective implementation of the intervention as illustrated in the Fig 1.

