#### Setting

This phase will be conducted in Dodoma and Singida. In Dodoma, the study will be conducted in Dodoma Regional Referral Hospital (DRRH), where an intervention group (nurse midwives and post-CS mothers) will be obtained. The DRRH provides both Basic Emergency Obstetrics and Newborn Care (BEmONC) and Comprehensive Emergency Obstetrics and Newborn Care (CEmONC) services. It has a separate maternity block for providing maternal and child health services. DRRH will be purposively selected as an interventional hospital because of the recently reported high rate of SSI due to CS [19]. In 2020, DRRH had 9016 total deliveries and the rate of CS was 28.7% (anecdotal evidence).

In Singida, the study will take place at Singida Regional Referral Hospital (SRRH). In SRRH, the control group will be obtained. The SRRH matches with DRRH in the sense that both are referral hospitals in the central zone of Tanzania where most of the complicated cases are managed. Both hospitals provide CEmONC including CS, and they have separate maternity blocks. In 2020, SRRH had a total of 3656 deliveries with a CS rate of 33.5% (anecdotal evidence).

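### Intervention mothers' baseline knowledge may be contaminated, because the guide is taught daily on the ward where later participants wait and the baseline test is timed only relative to a mother's own session

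*Protocol article*

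**What the plan says.** The relevant statements are spread over several sections of the protocol article.

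- **Timing of the test** (Assessment and education of post-caesarean mothers): the protocol states "Before the intervention, the pre-tested tool will be used by the researcher and RA to assess baseline knowledge of post-CS mothers", and "Both the assessment and intervention of post-CS mothers will be done before discharge". No other time is given.
- **Who is taught, and how often** (same section): "The education intervention about home care will be given in one group depending on the number of post-CS discharged on that day", and "This will be performed every day before discharge until the sample size is met". The session uses projected slides, a question round and "distribution of leaflets with simplified Swahili language and pictures demonstrating recommended home practices after CS".
- **Where** (Conceptual framework): "The inner environment is post-CS ward where education intervention will primarily take place". The section on training nurse midwives, by contrast, names a hospital meeting room for the nurses.
- **Length of stay** (Introduction): "most post-caesarean section mothers are typically discharged home within 48 hours".
- **Controls** (Assessment and training of nurse midwives): control mothers get a baseline test before discharge but no contact with the guide.
- **Analysis**: mothers' knowledge, scored adequate or inadequate, goes into a GEE for repeated measures. The intervention effect between groups is assessed by difference in difference.

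**The concern.** A before-and-after contrast against controls assumes that the first measurement in each arm precedes exposure. Here the test precedes a mother's own session, but nothing ties it to the sessions held for mothers who left on earlier days. If those sessions take place on the ward where she is lying, she may have seen slides, overheard answers or looked at a neighbour's leaflet before she is tested. This can happen in the intervention hospital only.

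Knowledge picked up in this way is counted as baseline and subtracted from the effect. A larger sample does not remove it, and the analysis cannot examine it unless earlier exposure was recorded. The baseline matters more than usual in this study. There is one purposively chosen hospital per arm, so baseline adjustment is the main protection against pre-existing differences in knowledge.

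**Working it through.** **Plan's own figure.** The protocol gives no figure for contamination and none for mothers' knowledge. The only figure needed is the number of mothers to be taught. Sample estimation, as worked there: 2 × (1.96√(0.16 × 0.84) + 0.8√(0.049 × 0.951)) / 0.111² = 144.7, stated as 145. With 5% attrition, 145 × 1.05 = 152.25, stated as 152. The figures reproduce from the formula as printed; whether that formula is sound does not bear on this point.

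**Opportunity for exposure.** Setting: "In 2020, DRRH had 9016 total deliveries and the rate of CS was 28.7" per cent.

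- 9016 × 0.287 = 2588 a year; 2588 / 365 = 7.1 caesareans a day.
- 152 / 7.1 = about 21 days of daily sessions at the least, if every mother is eligible and takes part.
- With stays of 48 hours, 2 × 7.1 = about 14 post-CS mothers are on the ward at once.
- A 48-hour window with one session every 24 hours holds two sessions, or three if sessions fall on both edges. The last is the mother's own, so she is present for one earlier session, or at most two. A stay of 24 hours may give none.

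The opportunity therefore exists for most mothers after the first days if stays are near 48 hours. It affects the baseline only if the test comes after the earlier session, which the wording allows but does not require.

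**Effect on the estimate, under assumption.** Let k be the share of the true gain already present at baseline, averaged over the arm. It equals the proportion of mothers exposed times the share of the full effect they have absorbed. With day-30 knowledge and controls unchanged:

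measured gain = (p1 − p0) × (1 − k)

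The protocol gives neither k nor a knowledge rate for mothers. For illustration only, I borrow the nurse-midwives' 44.8% and 63.4% from Sample estimation, a gain of 18.6 points. Approximate power for the difference in difference uses 145 and 290 mothers, controls flat at 44.8%, and an assumed within-mother correlation ρ of 0 or 0.3. With v(p) = p(1 − p), p_b the measured baseline, p1 = 0.634 and p0 = 0.448:

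variance = [v(p1) + v(p_b) − 2ρ√(v(p1)v(p_b))] / 145 + 2v(p0)(1 − ρ) / 290

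power = Φ(measured gain / √variance − 1.96)

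| k | Measured baseline | Measured gain (points) | Odds ratio | Power, ρ = 0 | Power, ρ = 0.3 |
|---|---|---|---|---|---|
| 0 | 44.80% | 18.60 | 2.13 | 75% | 88% |
| 0.10 | 46.66% | 16.74 | 1.98 | 66% | 81% |
| 0.25 | 49.45% | 13.95 | 1.77 | 50% | 65% |
| 0.50 | 54.10% | 9.30 | 1.47 | 26% | 35% |

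The table shows how sensitive the result is to k. It does not estimate k.

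**Passages that disagree.** The Conceptual framework has nurses trained first, and mothers then taught by those nurses. The Intervention section has the researcher and research assistants teach the mothers, with nurses trained afterwards. If the first order were followed, trained ward staff would be a second route by which the guide could reach mothers before baseline.

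**The case against.** The case on the other side is substantial.

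- **Spill-over is inferred.** No section says that waiting mothers attend, overhear or read the leaflet. Sessions are for that day's leavers, who take their leaflets home. This stands, and the point is therefore worded as a possibility.
- **The location is weakly documented.** It comes from a framework paragraph that the Intervention section departs from on who teaches and in what order. This also stands. But it is the only place named for the mothers' teaching, so the remedy includes reconciling it.
- **A condensed article leaves out the hour and room.** This is fair for routine detail. Here, though, the article itself combines ward teaching, daily repetition and a baseline timed only to the mother's own session.
- **The 48 hours is a general remark**, not a figure for the intervention hospital, and it is an upper limit. This stands.
- **The analysis may not carry the bias.** The difference-in-difference sentence sits under the SSI analysis, and how baseline enters the GEE is not spelt out. However, knowledge is the outcome for which a baseline is described, and the GEE is justified by repeated measurement of the same mother. An effect on change must use the baseline.
- **Partial learning may not cross the cut-off.** Adequate knowledge requires at least 75% of the maximum score, so overhearing part of a session need not reclassify anyone. A mother exposed twice might also score higher on day 30, offsetting the loss. Both stand.

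A reader might infer that the intervention baseline is certainly post-exposure, and that most of the effect is lost. For example, if 20% of inadequate mothers became adequate before baseline, from a true adequacy of 20%, the baseline would rise by 0.20 × 0.80 = 16 points, or 16 / 18.6 = 86% of the borrowed gain. The documents do not support this. The 20% is invented, and an 18.6-point gain from that baseline means the full session converts only 18.6 / 80 = 23% of inadequate mothers. The example thus gives bystanders nearly the whole benefit of the session.

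**Conclusion.** The point holds as a risk written into the procedure, not as a demonstrated bias. The documented combination lets a later participant meet the guide before her baseline, in the intervention arm only. Taken alone, this mechanism shrinks baseline-adjusted effects on mothers' knowledge. It does not touch SSI or a comparison of day-30 knowledge by itself.

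The relative loss equals k, which the protocol does not allow one to derive; it may be near zero. The figures at k = 0.10 to 0.50 rest on assumed k, a gain borrowed from nurse-midwives on another topic, an assumed correlation, and unchanged day-30 and control results. Nor is the net direction of all biases settled: the same team may teach and test, for instance, which could push the other way.

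**What to change.** In the section on assessment and education of post-caesarean mothers, choose one of two arrangements:

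1. Hold the session and hand out leaflets in a room away from waiting mothers, to that day's leavers only. The protocol already uses a hospital meeting room for the nurses.
2. Alternatively, test each mother before any session is held in her presence, at the same point of stay in both hospitals.

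Under either, add one tick-box recording whether she was on the ward during an earlier session, so that a sensitivity analysis is possible.

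Also reconcile the Conceptual framework with the Intervention section on where mothers are taught, who teaches them, and whether nurses are trained before or after them.

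The cost is small. The first option needs a room for about one hour a day. The second means that some mothers are tested closer to surgery, and before it is known who will be excluded for prolonged hospitalisation. The choice has to be made before enrolment, because unrecorded exposure cannot be recovered in the analysis.

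### At the intervention hospital the nurse-midwives' baseline knowledge test is placed after the mothers' teaching, which puts it at risk of partial contamination, and the Conceptual framework states the opposite order

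*Protocol article*

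**What the plan says.** All places are in the protocol article.

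- **Order (Intervention, part on nurse midwives):** "The intervention by nurse-midwives will be followed after the intervention of the post-CS woman".
- **Nurse baseline:** "Before the training, the pre-tested tool will be used to assess the baseline knowledge of nurses on post-CS home care". It belongs to the training session itself: "The intervention will take three hours including the time for pre-interventional assessment". The post-test follows at once: "Thereafter, they will be post-tested on the same day". No earlier nurse baseline is described.
- **Mothers' teaching (Intervention, part on post-caesarean mothers):** group sessions with slides, leaflets and questions. "This will be performed every day before discharge until the sample size is met". The teachers are named: "The researcher and other RA (nurse midwives in the profession) will be providing this education to post-CS mothers".
- **Place (Conceptual framework):** "The inner environment is post-CS ward where education intervention will primarily take place".
- **Control hospital (Intervention):** nurse-midwives and mothers at SRRH are not exposed to the guide's content until the mothers' sample is complete.
- **Opposite order (Conceptual framework):** "The implementation process will involve training nurse midwives first about the guide followed by the provision of education to post-CS mothers on home care", with the teaching done by the trained nurses.

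Nurse knowledge is part of the third Phase 4 objective. The design is a pre- and post-test with a non-equivalent control group. The analysis sections name GEE for knowledge and a difference-in-difference analysis for the effect between groups.

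**The concern.** A baseline in this design should be taken before the group has met the intervention. Under the order in the Intervention section, the guide has been taught daily at DRRH, mainly on the post-CS ward, for weeks before the nurses sit their first test. The knowledge tool is built from the guide (section on pre-testing prototype II), so contact with slides or leaflets bears directly on what is tested. Only the DRRH nurses could have this contact. A rise in their baseline would therefore not cancel against the control group and would be subtracted from the estimated gain.

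Under the order in the Conceptual framework, the problem moves to the mothers. Trained ward nurses could pass on the guide's content before the mothers' own pre-discharge baseline test. Neither order, as written, protects both baselines, and a baseline not taken before exposure cannot be taken later.

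**Working it through.** **1. The plan's own nurse figure.** The Sample estimation section uses 44.8% before and 63.4% after. The formula as printed gives 2 × {1.96 × √(0.634 × 0.366) + 0.8 × √(0.448 × 0.552)} / 0.186² = 2 × (1.96 × 0.4817 + 0.8 × 0.4973) / 0.034596 = 77.6. This rounds up to the stated 78. At the planned 1:2 ratio, 78 intervention nurses go with 156 controls before attrition. The planned gain is 63.4 − 44.8 = 18.6 points.

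**2. Time between first use of the guide and the nurse baseline.** The inputs are 9016 deliveries and a caesarean rate of 28.7% at DRRH in 2020 (Setting, marked there as anecdotal) and 152 intervention mothers (Sample estimation).

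- 9016 × 0.287 = 2588 caesareans per year; 2588 / 365 = 7.09 per day.
- 152 / 7.09 = 21.4 days if every caesarean mother is enrolled.
- If only half are eligible, sampled and willing (an assumption): 304 / 7.09 = 42.9 days.

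So 21 days is a lower bound at 2020 volumes.

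**3. Effect on the estimate.** Let d be the rise in DRRH nurses' baseline adequacy, in points, caused by earlier contact. With the post-test held at 63.4% and control nurses unchanged, the measured difference-in-difference is 18.6 − d. On the odds-ratio scale that a GEE would report, 63.4% against 44.8% gives 2.13; against 49.8% (d = 5) it gives 1.75. The documents give no value for d.

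**4. Illustration of power, under stated assumptions.** Difference-in-difference, normal approximation, two-sided 5%, 78 and 156 nurses, control flat at 44.8% at both times, post-test 63.4%, and within-nurse correlation ρ (assumed). With b = 0.448 + d as a proportion:

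- Variance, intervention: [b(1−b) + 0.634 × 0.366 − 2ρ√(b(1−b) × 0.634 × 0.366)] / 78
- Variance, control: 2 × 0.448 × 0.552 × (1−ρ) / 156
- Power = Φ(gain / SE − 1.96)

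Example, d = 0 and ρ = 0.5: the variances are 0.003074 and 0.001585, SE = 0.0683, 0.186 / 0.0683 = 2.72, power 0.78.

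| Assumed pick-up (points) | Measured gain (points) | Power, ρ = 0.5 | Power, ρ = 0.3 |
|---|---|---|---|
| 0 | 18.6 | 0.78 | 0.63 |
| 3 | 15.6 | 0.63 | 0.49 |
| 5 | 13.6 | 0.51 | 0.39 |
| 8 | 10.6 | 0.34 | 0.26 |

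The pick-up is applied to the intervention nurses' baseline only. The control proportion stays at 44.8%, because the SRRH nurses are the unexposed group.

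**The case against.** - **Exposure is inferred.** A reader might conclude that the DRRH baseline is certainly contaminated and the nurse result certainly biased. The documents do not support that. Teaching is by the researcher and research assistants, leaflets are for mothers, and no passage says that staff nurses sit in or read the material. The early meeting with the nurse in charge concerns organisation, not content. This stands, although nothing keeps staff nurses away either.
- **Exposure would be partial.** The Intervention section treats nurses working on the post-natal ward as a subgroup, and matching is on experience in a maternity unit. Adequate knowledge requires 75% of the maximum score, so casual contact need not carry a nurse over the threshold. This stands.
- **The order is not fully settled.** The explicit statement that nurse training waits for the mothers' sample is made for the control hospital. For DRRH it follows from reading the two parts of the Intervention section together, and the figure describing implementation is not shown. This stands, hence the word probably.
- **Another comparison survives.** A reader might also infer that the nurse objective is lost. It is not. The Intervention section compares knowledge between groups, and a chi-square test on post-intervention knowledge is planned; neither is lowered by a raised baseline. The error also runs towards zero, so it cannot create a false benefit. Against this, the hospitals are non-equivalent by design, and the baseline is what makes a comparison between them interpretable.
- **The order protects the mothers' outcomes.** Teaching mothers before training ward nurses keeps the mothers' baseline clean. This stands, and the fix keeps that order.

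**Conclusion.** The point holds as a risk, not as a demonstrated bias. Read together, the sections probably place the DRRH nurse baseline at least about 21 days after the guide came into use at that hospital, with no matching exposure at SRRH. Any pick-up lowers a difference-in-difference estimate point for point and pulls a GEE estimate of change towards no effect. Its size is unknown. The power figures rest on assumed pick-ups of 3 to 8 points, an assumed correlation of 0.3 or 0.5, and the sample-size proportions; they show sensitivity and predict nothing. Separately, and without any assumption, the Conceptual framework and the Intervention section contradict each other on which group comes first, and the choice decides which baseline is at risk.

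**What to change.** 1. Give the nurse-midwives' baseline questionnaire at both hospitals before the first mothers' session at DRRH, as a sitting separate from the training.
2. Keep DRRH nurse training after the last DRRH mother has had her baseline test and teaching, which is the order the Intervention section already sets.
3. Reconcile the Conceptual framework with the Intervention section so that one order governs.

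This uses the same questionnaire and must be settled before Phase 4 teaching begins. It costs an extra sitting, possibly spread over two days, since the plan itself expects difficulty in gathering all nurses on one day. The gap between nurse pre-test and post-test grows from one day to several weeks, with some risk of losing paired nurses beyond the 5% attrition allowed.

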**Methodology:**

This is a sequential exploratory mixed-method interventional study conducted in two regional referral hospitals in central Tanzania. A qualitative study will be conducted to explore the experiences of nurse midwives, mothers who had caesarean deliveries and their caretakers regarding the care of mothers and newborns at home. The findings will inform the development of a post-CS home care guide. Following a series of validations of the guide, research assistants will employ the guidelines to instruct post-CS mothers about home care as part of the intervention. Thirty participants will purposively be recruited for the qualitative study and a random sample of 248 nurse-midwives and 414 post-CS mothers to assess the effectiveness of the guide in improving knowledge of home care and preventing SSI. SPSS version 25 will be used to analyse quantitative data and content analysis, and ATLAS.ti will guide in analysing the qualitative data.

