p1 = Proportion after the intervention = 4.9% (0.049)

With a 5% attrition rate:

$$n=2\{1.96\sqrt{\left[0.16(1-0.16)\right]}+0.8\sqrt{\left[0.049(1-0.049)]\right\}}/{\left(0.16‐0.049\right)}^{2}$$

n = 145 plus 5% attrition rate 152

So, the minimum sample size is 145 plus a 5% attrition rate = 152

The ratio of the intervention group to the control group will be 1:2. Therefore, the control group sample size will be 304.

Therefore, the total sample size in this [40] study will be 456 post-CS mothers.

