#### Ethical issues

Prior to the start of the study, ethical clearance and approval will be obtained from the Muhimbili University of Health and Allied Sciences (MUHAS) Institutional Board Review (IRB). Then, permission to conduct the study will be obtained from TAMISEMI, Regional Medical Office (RMO), District Medical Office (DMO) and lastly, from the medical officer and ward in charge, where the study participants will be obtained. The informed consent will be obtained and signed by all participants after the aim of the study has been explained to them, along with benefits and harm (if any). The confidentiality of the participants in the data will be highly maintained. To achieve this, confidential identification numbers will replace the names of post-CS mothers and will only be available to the PI and supervisors. Mothers who will have SSI and post-partum anaemia will be referred to be reviewed by a doctor for further treatment and follow-up.

Nurse midwives and post-CS mothers in the control group will be exposed to the guide after the study. This will be done to ensure equal benefits for both interventional and control groups.

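### The Intervention section lets control-hospital nurses be trained on the guide once enrolment is met, before the last control mothers' day-30 outcomes, while Ethical issues puts control exposure after the study

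*Protocol article*

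**What the plan says.** All places are in the Phase 4 part of the protocol article unless noted.

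- **Intervention, control-arm paragraphs.** SRRH nurses and mothers do not receive the guide and continue with usual care. "The control group will also be assessed for baseline knowledge of home care after CS", and for mothers this test comes before discharge, as in the intervention arm. Knowledge and SSI status are then compared between arms.
- **Intervention, release of the guide to the control hospital.** For equal treatment, control nurses are to be trained on the guide and on "how to deliver the content to post-CS mothers after meeting the sample size of post-CS". They must then teach it to mothers.
- **Ethical issues.** "Nurse midwives and post-CS mothers in the control group will be exposed to the guide after the study".
- **Intervention, follow-up of mothers.** Mothers return to the facility where they delivered on days 7, 14 and 30. Wounds are assessed at these visits, and the knowledge post-test is on day 30.
- **SSI definition.** SSI is assessed on the same three days, with no restriction to one arm.
- **Intervention, DRRH nurses.** After their training, "Thereafter, they will be post-tested on the same day".
- **Sample estimation.** "The ratio of the intervention group to the control group will be 1:2. Therefore, the control group sample size will be 304".

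**The concern.** The two statements about when the control hospital receives the guide give different dates. The Intervention section ties it to reaching the sample size. Ethical issues ties it to the end of the study. Because the outcomes run to day 30, the end of enrolment is about a month before the end of follow-up.

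Whether the Intervention wording means enrolment can be judged from the article's own usage. In the same section, the education session is repeated each day before discharge up to the point where the sample size is reached. Under Sampling and method, participants are drawn until the target number is obtained. Both can only describe recruitment. The natural reading of the control clause is therefore the end of recruitment.

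On that reading, SRRH staff could be trained and told to teach the guide while recently enrolled control mothers still have visits at that hospital. The comparison rests on one intervention hospital and one control hospital. If the guide reaches control mothers before their outcomes are taken, the analysis cannot undo it. If the guide works, the effect would be to narrow the difference in SSI and in day-30 knowledge.

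**Working it through.** **Step 1. Reproduce the plan's control sample size.** Inputs from Sample estimation: proportions 0.16 and 0.049, multipliers 1.96 and 0.8, attrition 5%, ratio 1:2. With the formula as printed:

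2 × {1.96 × √(0.16 × 0.84) + 0.8 × √(0.049 × 0.951)} / (0.111)² = 144.7, rounded to 145.

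145 × 1.05 = 152 in the intervention arm; 152 × 2 = 304 controls; 152 + 304 = 456. The stated figures are reproduced. This checks only the count used below and does not endorse the formula. The abstract gives a different total, "a random sample of 248 nurse-midwives and 414 post-CS mothers", which at 1:2 means 276 control mothers.

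**Step 2. Rate of caesareans at the control hospital.** Setting gives 3656 deliveries at SRRH in 2020 and a caesarean rate of 33.5%.

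3656 × 0.335 = 1225 per year; 1225 / 365 = 3.36 per day.

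**Step 3. Control mothers still in follow-up when the target is met.** With even accrual and a fraction f of caesarean mothers enrolled:

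share = (3.36 × f × 30) / 304.

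The article gives no value for f, so the table shows an assumed range.

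| f (assumed) | Mothers within 30 days of CS | Share of 304 |
|---|---|---|
| 100% | 101 | 33.1% |
| 80% | 81 | 26.5% |
| 50% | 50 | 16.6% |
| 25% | 25 | 8.3% |

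With 276 controls, the ceiling is 101 / 276 = 36.5%.

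**Step 4. In follow-up is not the same as exposed.** The guide is taught in a session before discharge, and the Introduction says most mothers leave within 48 hours. On a 48-hour stay, the mothers still in the ward when the target is met number about 3.36 × 2 = 7, or 7 / 304 = 2%, even at full enrolment. The others would be at home and could meet trained staff only at return visits. The article does not say that the guide is taught at those visits. The step 3 shares are therefore upper limits on the mothers who could be reached.

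**The case against.** The strongest reply is that the two statements can both be met. The Intervention clause gives an earliest point for training and does not say that training starts at once, while Ethical issues already contains the safeguard. This is fair as a description of what the trial team may intend. It does not remove the need to align the text: whoever runs the control site from the Intervention section would be following it if they trained staff on the day recruitment closed.

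The second reply concerns the route of contamination, and most of it stands. Teaching happens before discharge, most late-enrolled mothers would be home, and wound assessments are done by the researchers and research assistants. For SSI, under even accrual, mothers still in follow-up would on average be halfway through their 30 days. Exclusions, matching and random sampling also push the enrolled fraction below 100%.

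Three stronger readings are tempting and are not supported:

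- *The control arm has only a baseline test.* Only the baseline knowledge test has a stated time for controls. However, the Phase 4 Study design is pre- and post-test with a control group, the Intervention section commits to comparing knowledge and SSI between arms, the SSI visits are not arm-specific, and the knowledge analysis uses repeated measurements.
- *A third of control mothers would be contaminated, and the knowledge effect diluted in proportion.* This treats every mother in follow-up as having received the full benefit of a pre-discharge session that she did not attend.
- *The nurse comparison is invalid because the control nurses' post-test has no stated time.* The article says that control nurses are not exposed to the guide, so a post-test after training would breach its own design. The exact time is detail that an article may leave to the full protocol or to Fig 3, which is not shown.

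**Conclusion.** The point holds as an inconsistency with a limited but avoidable consequence. The Intervention section, read with the article's own usage, releases the guide to the only control hospital at the end of enrolment. Ethical issues says after the study. The two must be reconciled.

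The number of control mothers still awaiting outcomes at that moment is at most about 101 of 304 (33%), and about 8% to 27% if 25% to 80% of caesarean mothers are enrolled. This rests on the 2020 SRRH volume, even accrual and an assumed enrolment fraction. The number actually exposed would be smaller and cannot be derived from the article. Any resulting bias would be toward no difference, on the premise that the guide is beneficial. Moderate severity is appropriate: the text should be corrected, but the flaw does not by itself undermine the trial.

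**What to change.** In the control-arm paragraph of the Intervention section, replace the condition tied to meeting the mothers' sample size with: *after the last control mother has completed her day-30 assessment and the control nurses have completed their post-test*. This agrees with Ethical issues, which can stay as it is.

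The cost is one clause of text and a delay of about 30 days before SRRH staff are trained. Sample size, visits and analysis do not change.
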